### Outcomes {12}

The primary outcome measured in this study will be the average reduction in malaria infection prevalence in children ≤ 5 years of age from baseline to month 12, as measured by RDT and microscopy. Secondary outcome measures include:
CDC light trap indoor density for anophelines and by anopheline species, as measured by light trap collections from 7 pm to 7 am on a 6 monthly basis. Change in mosquito density at baseline and month 12 between arms will be analysed by negative binomial regression with a random effect for study cluster.Anopheline-human contact (indoor and outdoor) using human biting rate (HBR) as an indicator for all anophelines and by anopheline species, as measured by HLC during 6-h intervals on a 6-monthly basis. Change in HBR at baseline and month 12 between arms will be analysed by negative binomial regression with a random effect for study cluster.Anopheline infectivity using sporozoite rate as an indicator for all anopheline and by anopheline species, as measured by laboratory detection of sporozoites in mosquito heads and thoraces from a subsample of anophelines collected during CDC light trap and HLC collections.Insecticide resistance, as measured by WHO tube test bioassay, during the intervention phase. Confirmed resistance, possible resistance and susceptibility will be calculated through evaluating knockdown and mortality rates.Subject behaviour and household features related to exposure to malaria and use of existing control tools, as measured by quantitative and qualitative surveys on a 6-monthly basis. Survey outputs will be summarised using basic statistics.Concentration of transfluthrin in air over the duration of an evening’s use or the Mossie-GO™ and the impact of indoor temperature on the concentration, as measured by air sampling at months 9 and 12. Mean concentration will be compared between arms.Acceptability of Mossie-GO™ in these communities, as measured be quantitative and qualitative surveys at 6 and 12 months and FGDs at 12 months. Outputs will be summarised using basic statistics and thematic analysis.Safety of intervention through monitoring of AEs and SAEs. Measured actively and passively throughout the duration of the study and total number of events and type of events will be compared between study arms.

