### Participant timeline {13}

**Table Tabb:** 

Month	Study period				
	Enrolment/Baseline data collection	Intervention			Close out
	0 (June 2024)	6 (Dec 2024)	9 (March 2025)	12 (June 2025)	July–Oct 2025
*Enrolment:*					
Household enrolment	X				
Device distribution	X				
U5 eligibility screen	X				
U5 enrolment	X				
Baseline U5 blood sampling	X				
Household survey	X				
CDC light trapping enrolment	X				
Baseline CDC light trapping	X				
HLC enrolment	X				
Baseline HLCs	X				
Air sampling enrolment			X		
*Intervention:*					
Blood sampling		X		X	
Household survey		X		X	
CDC light trapping		X		X	
HLCs		X		X	
Insecticide resistance sampling				X	
Air sampling			X	X	
Acceptability survey		X		X	
FGDs				X	
*Assessments:*					
Final analysis					X
Dissemination of results within community					X

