##### Entomological monitoring

Within each of the 56 clusters, CDC light trap collections will be conducted in 7 households from 7 pm–7 am at baseline, 6 and 12 months to allow assessment of the impact of intervention on the density of *Anopheles* mosquitoes indoors. Data collectors will be trained in setting up and taking down CDC light traps and heads of households may be trained to switch on/off the traps at the required time when necessary. Households will be selected at random for CDC light trapping at each timepoint. Additionally, HLCs will be performed indoors and outdoors for 3 consecutive nights in 3 households within each of 10 clusters (30 households total) at baseline, 6 and 12 months to determine the effect of the intervention on the host seeking behaviour of mosquitoes. Alongside the data collector, the head of household and community members will be trained to conduct the HLC and will be supervised during data collection. The clusters and households selected for HLCs will be selected at random for each time point.

Caught mosquitoes from CDC light trapping and HLCs will be examined to record vector species diversity, density and sporozoite rates at each time point. To characterize the insecticide resistance profile of the vector population in the study area, a series of WHO tube tests will be conducted in both districts (Jinja and Buikwe). Larval dipping will be conducted at selected sites, with larvae reared to adults in laboratory facilities and tested for insecticide resistance following WHO protocols and using standard WHO data collection forms [24].

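### The month-6 light-trap and landing-catch round has no stated role in the between-arm analyses of mosquito density and human biting rate, which name only baseline and month 12

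*Protocol article*

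**What the plan says.** Outcomes {12} defines both entomological outcomes as repeated six-monthly measures: light-trap density "as measured by light trap collections from 7 pm to 7 am on a 6 monthly basis", and HBR "as measured by HLC during 6-h intervals on a 6-monthly basis". It then names the analysis for each. For density: "Change in mosquito density at baseline and month 12 between arms will be analysed by negative binomial regression", with a random cluster effect. For HBR: "Change in HBR at baseline and month 12 between arms will be analysed by negative binomial regression with a random effect for study cluster". Month 6 appears in neither sentence.

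Trial design {8}, Participant timeline {13} and Entomological monitoring all schedule light traps and HLCs at month 6. Entomological monitoring says the traps run "at baseline, 6 and 12 months to allow assessment of the impact of intervention on the density" of *Anopheles* indoors, and that catches are examined for species, density and sporozoites at every time point.

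The section on statistical analysis of the secondary endpoints describes a negative binomial model for density with a random cluster effect. It names no time point and does not mention HBR separately. The Sample size {14} section says entomological numbers were set by logistics, budget and staffing. It gives no power figure for them.

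**The concern.** The plan collects a follow-up round in order to assess impact and then names analyses that do not use it. This is not a detail left open: Outcomes {12} states the time points, twice, and no other section gives month 6 a part in a between-arm comparison of density or HBR.

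Precision is at stake on secondary outcomes. The entomology is meant to help explain the epidemiological result, and its sample size was fixed by resources rather than by power. Omitting a round already paid for widens its intervals. Season is at stake too. Study setting {9} puts transmission peaks in March–May and September–November, and the timeline puts baseline and month 12 in June and month 6 in December. Month 6 is therefore the only post-intervention entomology round that follows the September–November peak.

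**Working it through.** **Counts (inputs from the consent section {26a} and Entomological monitoring).**
- Light traps: 7 households × 56 clusters = 392 per round, which reproduces the article's figure. Post-intervention rounds are months 6 and 12, so 2 × 392 = 784, and month 6 is 392/784 = 50%.
- HLCs: 3 households × 10 clusters = 30 per round, which also reproduces the article's figure. Over 3 nights this is 90 household-nights per round and 180 over both follow-up rounds, so month 6 is 90/180 = 50%. Each is done indoors and outdoors.

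The article gives no entomological power or variance figure, so the precision effects below rest on assumptions.

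**Light traps, all 56 clusters measured at every round.** Assume equal variance of cluster values at each round (set to 1) and equal correlation r between any two rounds.

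*Change from baseline, the analysis named in Outcomes {12}:*
- Month 12 minus baseline: 1 + 1 − 2r = 2(1 − r).
- Mean of months 6 and 12, minus baseline: (1 + r)/2 + 1 − 2r = 1.5(1 − r).
- Variance ratio 1.5/2 = 0.75 at every r. SE ratio √0.75 = 0.866, a fall of about 13%.

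*Adjusting for baseline in both analyses:*
- Month 12 alone: 1 − r².
- Mean of months 6 and 12: (1 + r)/2 − r².
- r = 0.2: 0.56/0.96 = 0.583, SE ratio 0.764, a fall of about 24%.
- r = 0.8: 0.26/0.36 = 0.722, SE ratio 0.850, a fall of about 15%.

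*Sensitivity check without any use of baseline.* Variance of the log rate ratio for month 12 alone = (2/28) × [s² + (1/mean + d)/7]. Here s² = ln(1 + CV²), d is the negative binomial dispersion and CV is the between-cluster coefficient of variation. For both rounds averaged, s² is multiplied by (1 + ρ)/2 and the second term is halved, where ρ is the between-round correlation of the cluster effects. The grid was mean catch 1 and 5; d 0.5 and 2; CV 0.3, 0.6 and 1.0; ρ 0.5 and 1.0, all assumed.
- Largest gain (mean 1, d = 2, CV 0.3, ρ = 0.5): SE 0.192 to 0.141, variance ratio 0.54.
- Smallest gain (mean 5, d = 0.5, CV 1.0, ρ = 1.0): SE 0.238 to 0.230, variance ratio 0.94.
- Over the grid, the SE ratio runs from about 0.74 to 0.97.

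**HLCs.** Entomological monitoring has clusters redrawn at random for each time point, so the repeated-measures formulas above do not apply. If each draw is a simple random 10 of 56, two draws share 10 × 10/56 = 1.8 clusters on average. Expected distinct post-intervention clusters rise from 10 to 20 − 1.8 = 18.2. By the same arithmetic, baseline and month 12 share only about 1.8 clusters, so the stated HBR change compares mostly different clusters.

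**The case against.** The strongest reply is that nothing is thrown away. Both outcomes are defined as six-monthly, month-6 catches are processed, the statistical methods section sets no time limit on the density model, and the analysis plan, which is not shown, may say how month 6 enters. Much of this stands. A reader might infer that month-6 data are discarded, or that half of all post-intervention entomology data is lost. The article supports neither. The sporozoite and species-composition analyses are not limited to month 12, and half the rounds is not half the information when the same clusters are measured again. The reply does not supply a role for month 6, however. Where time points for the density and HBR analyses are named, month 6 is left out.

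The second reply is that a baseline-to-month-12 contrast matches the window in the primary outcome definition, compares June with June, and answers a different question from an average of December and June. It is a legitimate contrast, and the article does not show it to be an error, though it also gives no seasonal reason for it. The abstract, moreover, has children sampled at both 6 and 12 months for the primary endpoint, so using both rounds is in keeping with the trial.

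Third, a reader might infer that season simply cancels because both arms are sampled together. Only a shared seasonal shift cancels. The background says active dispersal may be needed particularly when it is cooler, and a secondary objective relates indoor temperature to airborne transfluthrin. An effect of the device that varies by season is therefore possible, and a single averaged ratio would hide it.

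**Conclusion.** The point holds as one of stated time points. As written, the between-arm analyses of light-trap density and HBR omit the month-6 round, which is half of the post-intervention household-nights for each, and no other section gives it a part.

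For light traps, adding month 6 lowers the SE by about 13% for change scores, or by 24% (r = 0.2) to 15% (r = 0.8) with baseline adjustment. These figures assume equal variances and equal correlation between rounds, with r assumed. A comparison that ignores baseline gives a wider range, down to a gain of about 3%. For HLCs the support is a cluster count, 10 to about 18, and not a precision figure.

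The consequence is modest. Only secondary outcomes are affected, and the primary result does not depend on it.

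**What to change.** In Outcomes {12} and in the statistical methods for the secondary endpoints, state that months 6 and 12 are fitted in one negative binomial model with arm, round, arm-by-round and a random cluster effect. For light traps, add the cluster's baseline density as a covariate. Report the arm rate ratio averaged over both rounds together with the month-12 ratio, and show the month-6 ratio so that a seasonal difference can be seen. If the analysis plan already gives month 6 a role, bring the two sections into line with it. If month 6 is meant to be descriptive only, say so and why.

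The cost is analysis wording, with no new collection. The Trial status section has month 6 complete and month 12 still to come, and the statistician stays blinded until database lock, so the change can be made before unblinding. The downside is that the averaged ratio spans two seasons. If the device works differently by season, that will show only in the round-specific ratios, which are less precise.

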### Trial design {8}

This trial is a double-blinded placebo controlled cRCT with two arms. A total of 56 clusters will be randomly assigned, in a 1:1 ratio, to one of the two arms to receive the intervention or the placebo control. The intervention is a Mossie-GO™ device, containing a transfluthrin-treated disc which sits above a fan powered by solar energy (Fig. 1). The control arm will receive the Mossie-GO™ device with an identical looking disc with no active ingredient. All eligible, consenting households will receive a single Mossie-GO™ device with 5 W solar panel, and discs will be replaced at monthly intervals. The device requires 2 h charging time during the day and should be switched on in the evening and placed in the room where the child ≤ 5 years of age sleeps. If multiple children ≤ 5 years of age sleep in different locations, one location should be selected. If there are no children ≤ 5 years of age within the household, the Mossie-GO™ device can be placed in an alternative sleeping room.

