**Fig. 1 Fig1:**
[figure not shown]
Diagram of the Mossie-GO™ device (left), containing a fan and transfluthrin-treated or control disc, powered by a solar panel (right)

A survey will be conducted where 100 children ≤ 5 years of age in each cluster will be tested for malaria using RDTs and microscopy to determine malaria prevalence at baseline. Sampling will be repeated for 60 children ≤ 5 years of age in each cluster at 6 and 12 months. A household survey, classifying housing structure and collecting other variables which may impact the efficacy of the intervention, will be conducted within the sampled households. At the same timepoints, indoor CDC light traps will be installed in 7 households selected at random in each cluster and run from 7 pm to 7 am to collect mosquitoes. HLCs will be conducted over 3 consecutive nights indoors and outdoors of 3 households selected at random in 10 clusters. Households will only be eligible for HLC sampling if they have been selected for CDC sampling and sampling will be conducted on separate nights. Air sampling will also be conducted within the households selected for HLC sampling at months 9 and 12 to quantify the concentrations of transfluthrin in the air and to help inform entomological and epidemiological outcomes. Acceptability FGDs and surveys to understand barriers to use of the Mossie-GO™ device will also be conducted at months 6 and 12.

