## Sample size {14}

Data collected from the study region suggest prevalence of malaria infection by RDT in children ≤ 5 years of age is 20%. A conservative coefficient of variation (CV) of 0.5 for between cluster prevalence was assumed. To detect a 40% reduction in prevalence with 90% power, we need 28 clusters per arm and a sample of 100 children in each cluster. Due to budget restrictions, sample size was reduced after baseline to 60 children in each cluster at 6 and 12 months, resulting in 86% power.

Entomological sample sizes were determined based on logistics, considering budget and personnel restrictions. The sample sizes of similar studies were also considered. For CDC light trapping, sampling will be carried out in all clusters and randomised at the household level. HLCs will be randomised at both the cluster and household level.

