#### Statistical analysis of the secondary endpoints

For entomological outcomes, mosquito species composition will be reported as the total abundance and species-specific proportions of mosquitoes per sample per household per night. The outcomes will be compared across treatment arms. To address potential confounding factors and account for non-independence of data within clusters, logistic regression models will be employed, as described for the primary endpoint. Mosquito density will be reported as the total abundance of mosquitoes collected stratified by species. Additionally, for female *Anopheline* mosquitoes, the abundances will be broken down by blood fed/unfed, half gravid and fully gravid status. The outcomes will be compared across treatment arms. To address potential confounding factors and account for non-independence of data within clusters, a regression model will be employed with a negative-binomial log-link function to account for overdispersion typical of count data. These models will incorporate a random effect for each study cluster to adjust for intra-cluster correlation. Environmental covariates for factors, that were not controlled for with the allocation of clusters to trial arms, will be integrated into the models. These are average altitude and the distance from the nearest freshwater source per household, calculated from the mean spatial coordinate of each cluster. Comparative analyses will assess variations in mosquito species proportions across treatment arms to gauge effects of the intervention. Mosquito sporozoite rate will be reported as the proportion of mosquitoes (%) with sporozoites present per sample. The outcomes will be compared across treatment using the same linear regressions models employed for mosquito species composition. The prevalence of resistance to pyrethroids in *Anopheles* mosquitoes will be reported as the proportion of samples that are susceptible (98–100% resistance), possibly resistant (90–97% resistance) or confirmed resistant (less than 90% resistance) per sample. The outcomes will be compared across treatment arms. To address potential confounding factors and account for non-independence of data within clusters, logistic regression models will be employed, as described for the primary endpoint.

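### The biting-rate comparison rests on 10 redrawn clusters per round but is given the 56-cluster model; without a small-sample correction its false-positive rate is roughly 7–11%, not 5%

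*Protocol article*

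**What the plan says.** **Sampling.** The protocol article, section Entomological monitoring, states that "HLCs will be performed indoors and outdoors for 3 consecutive nights in 3 households within each of 10 clusters", at baseline, 6 and 12 months. The same section adds that "The clusters and households selected for HLCs will be selected at random for each time point". Sample size {14} says that "HLCs will be randomised at both the cluster and household level" and that the entomological sample sizes were set on logistics; no power, error rate, mosquito density or between-village variance is given for this outcome. Over the whole trial, "A total of 56 clusters will be randomly assigned, in a 1:1 ratio, to one of the two arms", but the protocol does not say that the 10 landing-catch clusters are balanced by arm.

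**Analysis.** Outcomes {12} states: "Change in HBR at baseline and month 12 between arms will be analysed by negative binomial regression with a random effect for study cluster". The sentence for light-trap density names the same model. The section on statistical analysis of the secondary endpoints gives the model a negative binomial log link and says: "These models will incorporate a random effect for each study cluster to adjust for intra-cluster correlation". It then says that altitude and distance to fresh water, both calculated from the cluster's mean coordinate, go into the models. No estimation method, test statistic, degrees of freedom or small-sample correction is stated.

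**The concern.** Arms are compared between villages, so the precision of the HBR comparison depends mainly on the number of villages. Three nights in the same three houses, indoors and outdoors, give 18 counts per village per round but add no villages. With so few clusters, ordinary large-sample inference from a random-effect model fails in two ways. Maximum likelihood (ML) underestimates the between-village variance, and a critical value of 1.96 ignores the few degrees of freedom left to estimate that variance. Both make the interval too narrow and the p-value too small.

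HBR is the plan's measure of human–vector contact, and the only one taken outdoors, in a trial motivated partly by outdoor-biting vectors. It is also to be reported by species, which gives further chances for a false positive.

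**Working it through.** **The plan's own figures.** The protocol states no error rate or power for HBR. Its only power figures are for the primary endpoint. With prevalence 0.20 against 0.12, between-cluster CV 0.5 and two-sided 5% (assumed), the usual formula for comparing cluster proportions gives 27.7, so 28, clusters per arm at 100 children, and 87% power at 60 children against the stated 86%. Those figures hold up but say nothing about HBR.

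**Inputs from the protocol.** 10 clusters per round; 3 houses × 3 nights × 2 positions = 18 counts per cluster per round; clusters redrawn each round; the comparison is change between baseline and month 12.

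**How many clusters enter.** Two independent draws of 10 from 56 share 10 × 10/56 = 1.8 clusters on average, so about 18–20 distinct clusters enter. An arm × time model has four fixed effects, which leaves 20 − 4 = 16 between-cluster degrees of freedom. A single-round comparison has 10 − 2 = 8.

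**Balanced theory.** With n clusters and df degrees of freedom, the false-positive rate against a normal reference is
- P(|t_df| > 1.96 × √(df/n)) with an ML variance;
- P(|t_df| > 1.96) with a REML-type variance.

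| Comparison | n | df | ML, z | REML-type, z |
|---|---|---|---|---|
| Change, clusters redrawn | 20 | 16 | 9.9% | 6.8% |
| Change, plus two cluster-level covariates | 20 | 14 | 12.3% | 7.0% |
| Single round, 5 v 5 | 10 | 8 | 11.8% | 8.6% |
| Contrast on all 56 clusters | 56 | 54 | 6.0% | 5.5% |

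Counting 18 distinct clusters instead of 20 is a rough allowance for overlap. It gives 10.6% (ML) or 7.0% (REML-type) without covariates (14 df), and 13.6% or 7.4% with them (12 df).

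**Simulation under no effect.** A negative binomial random-intercept model was fitted by ML to 18 counts per cluster per round, with 2,000 trials in each of six scenarios per design. Assumed values, none from the protocol: mean 3 or 0.5 per count, dispersion parameter 1 or 0.5, between-village SD 0.3–1.0 on the log scale, house SD 0 or 0.5, and an even split by arm. Monte Carlo error is about 0.7 points.

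| Design | Against z | Against t |
|---|---|---|
| Change, clusters redrawn | 7.6–10.8% | 5.9–8.2% (16 df) |
| Single round, 5 v 5 | 7.1–13.0% | 3.5–7.8% (8 df) |

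The lowest value in each row comes from the scenario with village SD 0.3 and sparse counts. The last column shows that a t reference placed on the ML standard error can still leave about 8%, so the variance estimate needs correcting too.

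**Split by arm.** An unrestricted draw of 10 from 28 + 28 gives exactly 5–5 in 27% of draws, and 3–7 or worse in 30%. The even split is therefore an assumption.

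**The case against.** The strongest reply is that the protocol names a model family and nothing more. Neither ML nor a Wald z test is mentioned, reference distributions and small-sample corrections are ordinary analysis-plan content, and a correction may stand in the analysis plan that is not shown. REML-type estimation with a t reference would comply with the quoted sentence. This stands in part: no error rate can be called a property of the plan as written. It does not dispose of the point, because the protocol fixes one model for a 56-cluster and a 10-cluster outcome without distinction, and the usual inference from that model is too narrow for the second.

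A reader might infer three stronger things that the documents do not support:

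- That the HBR test has a false-positive rate of about 12% on 8 degrees of freedom. That figure belongs to a single-round 5 v 5 contrast fitted by ML with a z test. The stated analysis is change from baseline on redrawn clusters, with about 16 degrees of freedom, and five per arm is not stated.
- That covariate adjustment takes it to about 18%. That uses 10 clusters and 6 degrees of freedom; with 20 clusters the same formula gives 12.3% (ML) or 7.0% (REML-type). The covariate sentence also follows the text on mosquito density and does not name HBR.
- That the primary or light-trap results share the problem. At 56 clusters the same calculation gives at most 6.0%.

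It is also fair to say that HBR is one of several secondary outcomes, with no success rule attached, and that indoor density is measured separately in all 56 clusters.

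**Conclusion.** The point holds, at moderate size. Without a small-sample correction, the stated change-from-baseline comparison of HBR would reject falsely in roughly 7–11% of trials at a nominal 5%. The low end corresponds to REML-type variance estimation with a normal reference, the high end to ML. A single-round contrast would run at about 7–13%, and adding the two cluster-level covariates puts the change analysis at about 7–12% on 20 clusters. All of this rests on assumed village variance, counts, estimation method and even split by arm. The direction is firmer than the number: every uncorrected version examined with redrawn clusters exceeded 5%. Whether the trial's actual HBR test will be too liberal depends on an inference method that this protocol does not state.

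**What to change.** Add a sentence for the landing-catch outcomes that keeps the arm × time (change) comparison and bases inference on clusters, by one of two routes:

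- a permutation test over cluster allocations that respects the redrawn clusters, so that a village drawn in both rounds keeps one arm label throughout; or
- REML-type variance estimation with a t reference on between-cluster degrees of freedom, about 16 for 20 clusters in an arm × time model and fewer with covariates.

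A t reference on the ML standard error alone is not enough. Leave altitude and water distance out of the landing-catch model, since each takes a scarce cluster-level degree of freedom. Reducing the data to one month-12 value per village and applying a two-sample t-test would drop the change comparison. Any cluster-level analysis on the log scale must say how a zero catch is handled, which matters most for the by-species results.

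The cost is analysis wording and a wider, correct interval: with 16 degrees of freedom the critical value is 2.12 instead of 1.96. Trial status shows month-12 collection still to come, and the statistician stays blinded until database lock, so the change can be made before results are known.
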